## Methods

### Study design

A parallel-assignment, multicenter randomized controlled trial will be carried out. Participants will be recruited from institutions providing eldercare services at home or in long-term facilities. In each of the institutions, and following baseline measurements, participants will be randomly assigned (1:1 ratio) through sealed opaque envelopes to either a control or experimental group by a coin-tossing sequence generation. Assessments of primary and secondary outcomes will be conducted at baseline and at 12 weeks (post-supervised phase) and 48 weeks (post-unsupervised phase) from the beginning of the intervention (Fig. 1). Outcome assessors and data analysts will be blinded to group allocation. Because of the nature of the study, blinding of the participants and the professional supervising the sessions is not possible. The study was designed, and the results will be reported according to the SPIRIT statement [30] and CONSORT guidelines for trials of nonpharmacologic treatment interventions [31].

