### Experimental group

#### Supervised phase

Participants in the experimental group will take part in a 12-week exercise intervention, consisting of two videoconference-supervised sessions per week of 45 min each. A minimum interval of 48 h will be ensured between sessions. The sessions will be carried out in groups of a maximum of 10 participants, implemented in the workplace but outside of working hours, and remotely supervised in real-time by a professional with previous experience in delivering group exercise sessions. Real-time videoconference platforms such as Webex (Cisco Systems, Milpitas, USA) will be used, and audio and video will be continuously shared between participants and trainer to allow complete bidirectional feedback (Fig. 2).

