### Sample size calculation

The sample size was calculated to detect a significant change in low back pain that could be relevant in terms of absenteeism from work [54]. Taking into account the average low back pain intensity of 5.0 ± 2.6 in the 0–10 NRS for pain observed in previous studies carried out by our research group in eldercare workers [55] and accepting an alpha error of 0.05 and a beta error of 0.20 in a bilateral contrast, 108 participants are necessary to detect a difference equal to or greater than 1 unit. The sample size has been increased by 20% due to expected dropouts. Therefore, the required sample will be 130 participants (65 in the control group and 65 in the experimental group).

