### Statistical analysis plan

IBM SPSS Statistics 27 statistical software package (SPSS, Inc., Chicago, IL) will be used for data analysis. Normality of distribution will be checked using the Kolmogorov‒Smirnov test, and non-normally distributed variables will be square-root transformed for statistical analysis. Continuous and categorical data will be reported as mean (standard deviation) and frequency (percentage), respectively. The primary analysis will be based on intention-to-treat, including data from all participants regardless of adherence to the intervention. Additionally, a per-protocol analysis will be performed, including only data from participants with ≥ 50% adherence. Finally, a post-hoc subgroup analysis will be performed to assess the effects of the intervention on low back pain outcomes separately in participants with (≥ 1 in average 0–10 NRS) and without (< 1 in average 0–10 NRS) low back pain at baseline. Between-group comparisons at baseline will be performed with the independent samples T and Chi-squared tests for continuous and categorical variables, respectively. For continuous variables, intervention effects will be analyzed with a group-by-time ANCOVA including baseline measurements as covariates. This ANCOVA will be performed separately to assess intervention effects in two time periods: 0 vs 12 weeks and 0 vs 48 weeks. Within-group changes in each time period will be performed with the paired samples T test. Effect size will be estimated by partial eta squared (η^2^). Values for η^2^of 0.02, 0.13, and 0.26 will be considered small, medium and large, respectively [56]. For categorical variables, intervention effects will be analyzed with McNemar’s test. The level of statistical significance will be set at *p* < 0.05.

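### The ANCOVA treats exercise-arm participants trained together in groups of up to 10 as independent; within-group correlation would make its standard errors too small, whereas omitting institution costs only precision

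*Protocol article*

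**What the plan says.** Under Study design, allocation is individual and is carried out institution by institution, once baseline has been assessed. The method is given as: "participants will be randomly assigned (1:1 ratio) through sealed opaque envelopes to either a control or experimental group by a coin-tossing sequence generation". No blocking or other restriction is described.

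Under Control group, controls receive no intervention. Under Supervised phase, the exercise arm trains together at the workplace for 12 weeks: "The sessions will be carried out in groups of a maximum of 10 participants". Under Unsupervised phase, participants exercise on their own from week 12 to week 48.

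Under Statistical analysis plan, for continuous outcomes "intervention effects will be analyzed with a group-by-time ANCOVA including baseline measurements as covariates". The model is run separately for baseline to 12 weeks and baseline to 48 weeks. Baseline measurements are the only covariates named. The Sample size calculation plans 65 per arm and makes no allowance for clustering.

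**The concern.** This is a partially nested design: one arm is treated in groups and the other is not. The article itself gives a reason to expect correlation within groups. Its Introduction argues that group dynamic and live supervision raise adherence and may thereby raise effectiveness. If the group influences adherence and response, two people from the same group are not independent pieces of evidence about the treatment. An ANCOVA that counts them as independent understates the variance of the exercise-arm mean, and with it the standard error of the primary comparison.

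Institution is a different matter. It affects both arms, because allocation is by individual within each institution. Leaving it out forgoes some precision and leaves any chance imbalance between institutions unadjusted.

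**Working it through.** **The plan's own figure.** The article says "108 participants are necessary to detect a difference equal to or greater than 1 unit", using "average low back pain intensity of 5.0 ± 2.6 in the 0–10 NRS for pain" and "accepting an alpha error of 0.05 and a beta error of 0.20 in a bilateral contrast". For independent observations the formula is 2 × [2.6 × (1.96 + 0.842) / 1]² = 106.1, that is 107 per arm or 214 in total. The stated 108 therefore matches a per-arm figure, not a total. The final step, 108 × 1.2 = 129.6, gives 130. The per-arm/total question is a separate point and nothing below depends on it. What matters here is that the calculation assumes independence.

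**Session groups: inputs.** Group size *m* is at most 10 (Supervised phase). Ten is a ceiling, so *m* = 5 is shown as well. The ICC is not given; 0.02, 0.05 and 0.10 are assumed. The relevant ICC is the residual one, after baseline adjustment. With 65 exercisers there are at least 7 groups (65/10 = 6.5).

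**Formulas.** The exercise-arm design effect is D = 1 + (*m* − 1) × ICC; the control arm has 1. With equal arms, the variance of the difference is multiplied by R = (D + 1)/2. The actual two-sided error of the naive test is 2 × [1 − Φ(1.96/√R)]. This is the error under no average effect, with groups varying around that average.

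| *m* | ICC | D | R | √R | Actual error of the 5% test |
|---|---|---|---|---|---|
| 5 | 0.02 | 1.08 | 1.04 | 1.02 | 5.5% |
| 5 | 0.05 | 1.20 | 1.10 | 1.05 | 6.2% |
| 5 | 0.10 | 1.40 | 1.20 | 1.10 | 7.4% |
| 10 | 0.02 | 1.18 | 1.09 | 1.04 | 6.0% |
| 10 | 0.05 | 1.45 | 1.225 | 1.11 | 7.7% |
| 10 | 0.10 | 1.90 | 1.45 | 1.20 | 10.4% |

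**Simulation check.** The set-up was 130 participants, 7 assumed institutions, coin-toss allocation, groups of at most 10, an unadjusted two-sample t-test and 6,000 runs. The error was 5.1% without clustering, and 6.1%, 7.0% and 9.6% at session-group ICC 0.02, 0.05 and 0.10. At the two higher ICCs this is a little below the formula for *m* = 10, as expected when not every group is full.

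**Institution.** In the same simulation, with no session-group effect and institution left out of the test, the error was 4.9% and 4.8% at institution ICC 0.05 and 0.10, so there is no inflation. On precision, removing an institution component of 5% or 10% of the variance would at best multiply the standard error by √0.95 = 0.975 or √0.90 = 0.949. The gain is smaller once degrees of freedom are spent, and smaller again where the baseline covariate already captures institution differences.

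**Allocation.** Under coin tossing with N = 130, P(exactly 65/65) = C(130,65)/2¹³⁰ = 7.0%, and the 95% range is 54 to 76 per arm. Relative efficiency is 4ab/130²: 0.994 at 60/70 and 0.971 at 54/76. With SD 2.6 and an assumed baseline correlation of about 0.71, power moves from 87.3% at 65/65 to 86.3% at 54/76.

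**The case against.** The strongest reply is that the size of the effect is unknown. The ICC is assumed, 10 is a maximum, dropout shrinks groups, and small institutions would supply few exercisers each. With groups of 5 and an ICC of 0.02 the error is 5.5%, which few would worry about. This stands, and it is why a range is given rather than one figure. It does not rescue the model, because the direction is the same throughout the range and the article's own rationale points to a group effect.

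A second reply is that a journal article condenses the full plan. Here, though, the article names the model, its covariates, the software and the significance level. The point is about a model that is stated, not about one left out.

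Third, groups stop meeting at week 12, so correlation at week 48 is less plausible. This also stands.

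Four stronger readings are tempting, and the documents do not support them:

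- *A reader might infer that omitting institution invalidates the test.* Unrestricted individual allocation imposes no such condition, and the simulated error stays at about 5%.
- *A reader might infer that coin tossing cannot give 65/65, or is unsound.* It is valid and can give that split; it only cannot guarantee it, and the power lost is about 1 point or less.
- *A reader might infer fixed groups, each with its own trainer.* The Supervised phase section gives a maximum size and a setting. It does not say that membership is fixed or how many trainers there are, and one trainer for all groups would not create correlation within groups.
- *A reader might take the 10.4% as the expected error rate.* It needs every group at the maximum and the highest ICC assumed.

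**Conclusion.** The concern holds for session groups. As written, the primary model treats participants trained together as independent, and any positive within-group correlation makes its standard errors too small. For assumed ICCs of 0.02 to 0.10, the nominal 5% test has an actual error of about 5.5% to 7.4% with groups of 5 and 6.0% to 10.4% with full groups of 10. These figures rest on equal arms, a common group size and a normal approximation, and they apply most plausibly at week 12.

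For institution the point is smaller: precision and chance imbalance, not validity. On allocation, 65/65 should be read as the expected split, with no material consequence for power. Overall this is a change that should be made before the final analysis, not a fatal flaw.

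**What to change.** - Add institution to every between-arm model.
- For the primary week-12 comparison, fit a partially nested mixed model: baseline as covariate, a random session-group intercept in the exercise arm only, each control as a singleton, and small-sample degrees of freedom, since there may be only about 7 groups. Use the same model at week 48.
- Where an institution has only one session group, institution may be fitted as a random effect so that both terms can be estimated.
- State that 65/65 is the expected split. Changing the randomisation method while the trial is running is not needed.

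The cost is mainly wording. Institution is known from randomisation, and attendance is recorded at each supervised session, so group membership should be recoverable. The statistical cost is wider confidence intervals: up to about 20% at ICC 0.10 with groups of 10 (√1.45 = 1.20), with small-sample degrees of freedom adding something to that, and about 2% at ICC 0.02 with groups of 5 (√1.04 = 1.02). With few groups, the session-group variance will itself be estimated imprecisely.

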#### Primary outcome

The primary outcome will be average pain intensity in the low back during the last 7 days, measured by the 0–10 Numerical Rating Scale (NRS) [41] ranging from 0 (complete absence of pain) to 10 (worst imaginable pain) (Table 2).

**Table 2 Tab2:** Detailed description of the outcome measures that will be assessed in the trial

Questionnaire/Test	Functions/Parameters	Description
**Musculoskeletal pain**^**a**^		
0–10 Numerical Rating Scale (NRS) for pain [41]	Pain intensity (average and worst)	Intensity during last 7 days (0–10)
Ad hoc question	Pain frequency	Days in pain during last 7 days (0–7)
Ad hoc question	Pain interference	Days in which pain negatively interferes with work during the last 7 days (0–7)
Ad hoc question	Pain medication consumption	Days of analgesic medication consumption during last 7 days (0–7)

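### The primary outcome has no designated time point and is tested at 12 and at 48 weeks, each at 0.05, with no testing order, success rule or adjustment

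*Protocol article*

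**What the plan says.** The Primary outcome section gives the measure and the recall period but no visit: "The primary outcome will be average pain intensity in the low back during the last 7 days". The Abstract does the same. Under Study design, primary and secondary outcomes are measured at baseline, at 12 weeks (end of the supervised phase) and at 48 weeks (end of the unsupervised phase).

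The Statistical analysis plan section then commits to two analyses: "This ANCOVA will be performed separately to assess intervention effects in two time periods: 0 vs 12 weeks and 0 vs 48 weeks". It sets one level for everything: "The level of statistical significance will be set at *p* < 0.05".

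The Sample size calculation names no visit and spends alpha once, "accepting an alpha error of 0.05 and a beta error of 0.20 in a bilateral contrast".

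The aim at the end of the Introduction covers medium-term and long-term effects together and ranks neither first. The only wording that might suggest a ranking is in the Discussion, where the 48-week follow-up is called additional in a list of strengths.

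**The concern.** The time point is part of what a primary outcome is. With two visits, two tests and no rule linking them, the article does not say which result decides whether the trial succeeded. The two visits also support different claims: one concerns the effect of supervised sessions, the other what remains after a further 36 weeks (48 − 12) of exercising alone. If the headline visit can be chosen once the results are known, both the claim and its error rate depend on the data. The 5% used to size the trial would then not describe the test actually relied on.

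**Working it through.** **Inputs from the article.** Two tests of the primary outcome, each two-sided at 0.05 (Statistical analysis plan). One two-sided alpha of 0.05 with power 0.80, a difference of 1 unit and an SD of 2.6 (Sample size calculation).

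**Input not in the article.** The correlation ρ between the 12-week and 48-week test statistics. It is treated as an assumption and varied from 0 to 0.9.

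**Step 1: the plan's own error rate.** For one test at 0.05, P(|Z| > 1.96) = 5.0%. The stated alpha is right for one test of the primary outcome at one visit.

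**Step 2: two tests, with a win at either visit counted.** If there is no effect at either visit, the chance of at least one false positive is

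1 − P(|Z₁| < 1.96 and |Z₂| < 1.96),

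where Z₁ and Z₂ are standard bivariate normal with correlation ρ. At ρ = 0 this is 1 − 0.95² = 9.75%. Other values:

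| ρ | At least one false positive |
|---|---|
| 0 | 9.75% |
| 0.3 | 9.51% |
| 0.5 | 9.07% |
| 0.7 | 8.35% |
| 0.8 | 7.81% |
| 0.9 | 7.04% |

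Every value in this range is above 5%.

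**Step 3: the same tests under other success rules.**

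- One named primary visit at 0.05: 5.0%.
- Both visits required: at most 5%, because a false claim needs a false positive at a visit with no true effect and each test is held at 0.05.
- Fixed order, with the second visit tested only if the first is significant: at most 5%. If the first null hypothesis is true, any false claim must begin with a rejection at the first visit. If it is false, only the second test can err, at 0.05.
- Bonferroni, 0.025 at each visit: 1 − 0.975² = 4.94% if independent, and 4.65% at ρ = 0.5.

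**Step 4: what Bonferroni would cost.** The required sample size scales with (z for alpha + z for power)². The ratio is ((2.241 + 0.842)/(1.960 + 0.842))² ≈ 1.21, or about 21% more participants. With the article's difference and SD, n per arm = 2 × 2.6² × (z for alpha + z for power)² / 1². This gives 107 per arm at 0.05 and 129 at 0.025.

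The 107 per arm does not match the article's 108 in total. That is a separate matter and does not affect the error rates above.

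**The case against.** The strongest reply is that no inflation is written into the plan. No section says that success at either visit is enough; if both had to be significant, the error rate would not exceed 5%. The two visits also answer different questions, and two questions reported separately at 0.05 need no joint error rate unless they are merged into one claim. The Discussion's description of the 48-week follow-up as additional could be read as making 12 weeks primary. A condensed article may also leave detail to a fuller plan, and the cited registration is not available here.

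Part of this stands. The 9% is conditional on an either-visit rule and an assumed correlation, so a flat statement that the trial's false-positive rate is 9% goes beyond the text. The point is also limited to what this article states. The rest does not remove the point. One primary outcome covers both visits, so the article does not set up two separate primary questions. The Discussion remark does not rank the visits, and the aim gives both horizons equal standing. The two separate tests and the single unadjusted level are stated in the article's own analysis section, so they are not details deferred elsewhere.

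A reader might also infer that the separate 48-week ANCOVA contradicts the intention-to-treat statement because people lost to follow-up would drop out of it. The documents do not support that. The sentence, "The primary analysis will be based on intention-to-treat, including data from all participants regardless of adherence to the intervention", concerns adherence, and the handling of missing values may sit in a fuller plan. Nor can a count of excluded participants be derived. Taking 20% of 130 gives 26, but the article's own allowance is 130 − 108 = 22, and it is not tied to either visit.

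**Conclusion.** The point holds in conditional form. The article fixes two unadjusted 0.05 tests of one primary outcome and gives no primary time point, order or success rule, while the sample size assumes one two-sided 0.05. Nothing written prevents either visit from carrying the primary claim. In that case the chance of at least one false positive is about 9% at an assumed correlation of 0.5, within a range of 7.0% (correlation 0.9) to 9.75% (independent). Without an adjustment or a fixed testing order, it stays within 5% only if one visit is primary or both must succeed. This should be corrected. It does not invalidate the design.

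**What to change.** Before outcome data are compared, name one primary time point and test it at two-sided 0.05. Twelve weeks, the end of the supervised phase, is a reasonable example, but the essential step is to choose one in advance. Test the other visit at 0.05 only if the first is significant; otherwise report it as an estimate with a confidence interval. State in the sample size section which visit the calculation refers to.

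The cost is wording. The Trial status section says recruitment is still active, so the change could be made in time. No participants are added and no power is lost at the first visit. The downside is that a failure at the first visit rules out a confirmatory claim at the second, which matters because the stated aim includes the long term. If the sponsor wants both visits to stand alone, Bonferroni is an alternative at about 21% more participants for the same power per test.

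Optionally, both contrasts could come from one repeated-measures mixed model, so that participants with any follow-up contribute. That is a refinement and is not needed to resolve the multiplicity.

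### The stated effect measure, partial eta squared with verbal bands, is not tied to the 1-point NRS target and would very probably label that target small

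*Protocol article*

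**What the plan says.** In the protocol article, the Sample size calculation section gives the aim of the calculation: "The sample size was calculated to detect a significant change in low back pain that could be relevant in terms of absenteeism from work". It assumes an "average low back pain intensity of 5.0 ± 2.6 in the 0–10 NRS" and concludes that "108 participants are necessary to detect a difference equal to or greater than 1 unit". The trial's own yardstick for the primary outcome is therefore 1 point on the pain scale.

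The Statistical analysis plan section uses another yardstick. Intervention effects on continuous outcomes come from a baseline-adjusted ANCOVA, run separately for 0 versus 12 weeks and 0 versus 48 weeks. Then: "Effect size will be estimated by partial eta squared", where values of 0.02, 0.13 and 0.26 "will be considered small, medium and large, respectively". No other effect measure is named for the between-group comparison. The same section says that continuous data will be summarised as mean and SD, and that variables failing a normality check will be square-root transformed for analysis.

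**The concern.** The section that sizes the trial and the section that describes how effects are measured do not refer to each other. The verbal bands apply to every continuous outcome, including the primary one, and are not calibrated to the difference the trial was built to detect. A result that exactly met the target could be reported as a small effect, with no statement of how many points were gained or how precisely.

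Three properties make partial eta squared a poor main measure here. It has no sign, so it does not say which group did better. It is not in NRS points. In an ANCOVA its value depends on how well baseline predicts follow-up, so an identical benefit in points can yield different values at the two time points.

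The validity of the test is not at stake. What is at stake is whether the planned effect measure lets the trial say that a 1-point benefit is supported or excluded.

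**Working it through.** **Inputs.** From Sample size calculation: difference 1 NRS unit, SD 2.6, two-sided alpha 0.05, power 0.80, equal arms. From Statistical analysis plan: bands 0.02, 0.13 and 0.26; ANCOVA with baseline as covariate. Assumed, because the article does not give it: the baseline-outcome correlation r, shown from 0 to 0.9. Also assumed: the SD of 2.6 applies at follow-up.

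**The plan's own figure.** For two independent means, n per arm = 2 × 2.6² × (1.960 + 0.842)² / 1² ≈ 106.1, so 107 per arm and 214 in total. The stated total of 108 is not reproduced from the stated inputs. It matches a per-arm number, or a total if an unstated r of about 0.70 is assumed. The inflation does reproduce: 108 × 1.2 = 129.6, or 130. The discrepancy in 108 is a separate matter and does not enter what follows, because the population value of partial eta squared does not depend on n.

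**Partial eta squared for a true 1-point difference.** Adjusting for baseline reduces the residual SD to 2.6 × √(1 − r²). With 1:1 allocation:

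- D² = (1/2.6)² / (1 − r²) = 0.1479 / (1 − r²)
- partial η² = D² / (D² + 4)

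| r (assumed) | D² | partial η² |
|---|---|---|
| 0 | 0.148 | 0.036 |
| 0.3 | 0.163 | 0.039 |
| 0.5 | 0.197 | 0.047 |
| 0.7 | 0.290 | 0.068 |
| 0.8 | 0.411 | 0.093 |
| 0.85 | 0.533 | 0.118 |
| 0.9 | 0.779 | 0.163 |

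Setting η² = 0.13 gives D² = 4 × 0.13 / 0.87 = 0.598, so 1 − r² = 0.1479 / 0.598 = 0.247 and r ≈ 0.87. Below that correlation the target lies between the small and medium values.

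**Differences in points that correspond to the bands.** Difference = 2.6 × √(1 − r²) × √(4η² / (1 − η²)):

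| η² | r = 0 | r = 0.5 | r = 0.7 |
|---|---|---|---|
| 0.02 | 0.74 | 0.64 | 0.53 |
| 0.13 | 2.01 | 1.74 | 1.44 |
| 0.26 | 3.08 | 2.67 | 2.20 |

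**Same benefit, different value.** If r were 0.7 at 12 weeks and 0.5 at 48 weeks, an unchanged 1-point benefit would move from 0.068 to 0.047.

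**Alternative reading of the model.** If the group-by-time wording meant an analysis of change scores, D² = 0.1479 / (2(1 − r)), and η² is 0.026, 0.036 and 0.058 at r = 0.3, 0.5 and 0.7. The label does not change.

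**What a confidence interval would add.** With 54 analysed per arm, the 95% half-width is about 1.96 × 2.6 × √(1 − r²) × √(2/54): 0.98 at r = 0 and 0.70 at r = 0.7. An observed 1-point difference would carry an interval of roughly 0.0 to 2.0, or 0.3 to 1.7. The label conveys none of this.

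**The case against.** A reader might infer that the result cannot be judged against the planned target at all. The documents do not support that. Means and SDs will be reported for continuous data, and they give direction and a raw between-group difference in points that can be set beside 1 unit. What they do not give directly is the adjusted estimate the trial tests, with its precision.

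A reader might also infer that the two sections contradict each other. They do not. One gives a difference to detect; the other gives conventional labels for a standardised measure. Nowhere does the article say that a small eta squared means an irrelevant effect, or that success will be judged by it. A difference of 1/2.6 = 0.385 SD can be small on a generic scale and still matter for absenteeism.

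Two further objections limit the size of the point. The correlation is undocumented, and the label depends on it. If the three values are read as benchmarks rather than lower cut-offs, the midpoint between small and medium is 0.075, and the target is nearer medium from r of about 0.74. It is also true that a condensed article may leave estimates and intervals to a fuller plan, so silence about a confidence interval is not itself an error.

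Finally, reporting the ANCOVA estimate in points is not automatic. If the square-root rule is triggered for the primary outcome, the model's estimate is no longer on the NRS scale. That is correct, and the fix has to deal with it.

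What remains does not rest on silence: the article positively chooses a measure and verbal bands for the primary outcome without reference to its own target.

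**Conclusion.** The point holds as a matter of interpretation and reporting, and it is minor. The named effect measure is not tied to the 1-unit target. Read as lower cut-offs, its bands would call that target small for any baseline-outcome correlation below about 0.87: η² is 0.036 unadjusted and 0.047 to 0.068 at assumed correlations of 0.5 to 0.7. This rests on the protocol's SD of 2.6 holding at follow-up and on equal arms. The finding is that the two yardsticks are unreconciled. It is not that they conflict, nor that the trial cannot be read against its target.

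**What to change.** State that the primary effect estimate is the baseline-adjusted between-group mean difference in NRS points, with a 95% CI, at 12 and at 48 weeks, read against the 1-unit difference in the sample size section. Obtain it from an ANCOVA on the untransformed 0–10 NRS, and treat any square-root-transformed analysis of this outcome as a sensitivity analysis. Keep partial eta squared only as a supplement, and drop the verbal labels for the primary outcome.

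No new data are needed. If the transformation rule is not triggered, the estimate comes from the ANCOVA already planned and the change is wording. If it is triggered, the primary outcome needs one additional untransformed analysis. The Trial status section says recruitment is still active, so the change can be recorded before results are known.
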